Circuit exercise has been found to improve stroke survivors’ functions and quality of life.^[10–16]^ However, the conventional form is seen as less enriched and lacking in fun. Training in enriched and fun environment can promote neuroplasticity, in addition to facilitate personalized motivation and cease stress and anxiety among stroke survivors.^[17–20]^ Nonetheless, no studies have incorporate design-for-fun games environment into the existing circuit exercise. Past studies about circuit exercise have also not included motivation and self-efficacy, 2 important determinants for recovery among stroke survivors^[21]^ in their assessment of intervention outcome despite the fact that stroke survivors frequently demonstrate decline in these component and affect their functional independence over time.^[21–26]^ There is a need to review the existing conventional circuit exercise and offer a more enriched environment by adding multisensory stimuli and cueing, limb integration and cognitive stimulation to further increased neuroplasticity potentials such as game-based circuit exercise.^[27]^ Therefore, the purpose of this study is to determine the effectiveness of game-based circuit exercise in comparison to conventional circuit exercise on functional outcome, motivation level, self-efficacy and quality of life among stroke survivors. This study also aims to assess whether the outcomes gained from the 2 interventions could be sustained at week 12 and week 24 post trial.

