### Study design and setting

2.1

This is an assessor-blinded randomized control trial which compare 2 types of intervention, namely game-based circuit exercise (experimental group) and conventional circuit exercise (control group). The study will be conducted at Hospital Putrajaya, a main referral center for stroke cases in Putrajaya, the federal administrative capital of Malaysia. Database of post-stroke patients which is maintained by the physiotherapy department of the hospital will be used to recruit participants adequately. The flow of the participants through the trial is as shown in the CONSORT diagram (Fig. 1).

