### Study participants

2.2

Eligible participants will be recruited by the main researcher using the following inclusion criteria:

1.Clinically diagnosed either hemorrhagic or ischemic stroke by a medical or neurology physician.2.Age 40 to 80 years old (to minimise risk of frailty which is prevalent in those above 80).^[28]^3.Able to perform basic activities of daily living such as walking and turning, stepping up and down steps with or without a walking aid and hold a glass full of water with the non-affected hand.

Exclusion criteria are:

1.Score below 20 on Montreal Cognitive Assessment (MoCA) which indicates the presence of cognitive impairment2.Presence of other neurology or medical conditions which limit physical function such as Parkinson's disease, severe musculoskeletal disorders, unstable angina or uncontrolled hypertension.3.Score 4 or more on a Modified Rankin Scale (4: moderate severe disability; 5: severe disability; 6: death)4.Attended by a home physiotherapist after discharged from in-patient setting or attending a traditional therapy.5.Has visual field defects

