Progression	Standing, alternate steps-ups on the 8-inches step board (Lifting up 2 kg of dumbbell/speed at 50 beats per min)	Walk & touch cones hexagon shape (follow rhythm)	Repeated double jab punching with squat (follow rhythm)
	**Standing; repeated heel raise**	**Backward walking**	**Cross straight**
Frequency	2 sessions/wk	2 sessions/wk	2 sessions/wk
Intensity	Speed at 70 beats per min	Speed at 45 beats per min	Speed at 100 beats per min
Time	1 min	1 min	1 min
Technique	Standing, alternate raises heel (without load)	Backward walking (follow rhythm)	Repeated cross straight punching (follow rhythm)
Progression	Standing, alternate raises heel (Lifting up 2 kg of dumbbell/speed at 75 beats per min)	Backward walking (follow rhythm for 2 min)	Repeated 4 times cross straight punching with squat (follow rhythm)

Meanwhile, participants in the control group will be supervised by 2 physiotherapists to perform the conventional circuit exercises in a group of 5 participants per session. The participants will take turn to perform exercise tasks which are organized in a total of 6 stations, consisted of;

1.cycling,2.repeated sit to stand,3.repeated arm curl,4.repeated hip & heel raise,5.stepping up and down and6.obstacle walking.

The exercise duration in each station is 5 minutes interspersed by a 2-minute rest. Similar to the experimental group, all participants in this control group will receive an exercise session of 40 minutes, twice per week for 12 weeks.

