### Sample size

2.7

The required sample size for this study was estimated using GPower software version 3.0.10. This study will use mixed model analysis of variance (ANOVA) to analyze time, group and interaction effects of the interventions. Therefore, F-test (ANOVA repeated measure, within-between interactions) was chosen and inputted into the system. The study power and alpha value was set at 80% and 0.05, respectively. Based on these inputs, a minimum sample of 82 subjects is required, that is, 41 participants in each trial group.

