### Data analysis

2.8

All data will be entered into IBM Statistical Packages for Social Sciences (SPSS) version 25.0. Intention-to-treat (ITT) analysis approach will be used; all the recruited participants will be included in the outcome analysis. Using ITT approach, missing data will be replaced with “last observation carried forward.” Socio-demography and health profile of the participants will be analyzed descriptively and reported as frequencies (percentages) and mean (standard deviation) or median (inter-quartile range). The effects of the interventions will be analyzed using mixed model ANOVA and reported as main time, group and time-group interaction effects for each outcome variable. Level of significance is set as *P* < .05 for all results.

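### Change over time is labelled an effect of the interventions, although both arms are treated and only the between-arm contrast is protected by randomisation

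*Protocol article*

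**What the plan says.** Section 2.8 (Data analysis) of the protocol article states: "The effects of the interventions will be analyzed using mixed model ANOVA". The results are to be "reported as main time, group and time-group interaction effects for each outcome variable", with P < .05 as the level for all results. Section 2.7 (Sample size) uses the same label, choosing the model "to analyze time, group and interaction effects of the interventions". The F-test entered for the sample size there is the within-between interaction.

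The Introduction gives a comparative first aim, game-based against conventional circuit exercise. It adds a second aim, to "assess whether the outcomes gained from the 2 interventions could be sustained at week 12 and week 24 post trial". The Abstract repeats both.

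Sections 2.1 and 2.4 describe two arms, both supervised and both exercising. In section 2.4, "all participants in this control group will receive an exercise session of 40 minutes, twice per week for 12 weeks", and the game-based arm has the same session length, frequency and duration. Section 2.6 sets four assessments: baseline, end of the 12-week programme, and 12 and 24 weeks after that. The stroke criterion in section 2.2 is "Clinically diagnosed either hemorrhagic or ischemic stroke by a medical or neurology physician". None of the listed criteria mentions time since stroke.

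**The concern.** Three model terms sit under one heading, effects of the interventions, but they do not carry the same information.

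- **Time-group interaction:** compares change between randomised arms. It is the only one of the three that directly estimates how the effect of one programme differs from the other.
- **Main time effect:** pools change across both arms. Without an untreated arm it contains whatever the programmes do, plus recovery, plus familiarity with tests repeated at four visits. Randomisation does not separate these.
- **Main group effect:** a between-arm contrast, but one averaged over all four visits, including a baseline at which randomised arms differ only by chance.

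No sentence makes the interaction the deciding term or limits how the time effect may be read. The second aim adds to the problem because it speaks of gains from both programmes. A trial with a significant time effect and no interaction could then be reported as showing that both programmes work and that their benefits last, even if neither did anything.

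**Working it through.** **Inputs from the protocol article:** 82 participants, 41 per arm (section 2.7); four visits (section 2.6); significance at 0.05 (section 2.8). The 82 is taken as given. The article states no effect size for it, so it cannot be reproduced, and the point does not depend on it.

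**Inputs assumed, because the article gives none:** a shift of d standard deviations, identical in both arms and present at all three post-baseline visits; equal correlation r between visits; no difference between arms.

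**Step 1, the main time effect.** The visit means are (0, d, d, d), with overall mean 0.75d. Their variance is

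f² = [(0.75d)² + 3 × (0.25d)²] / 4 = 0.1875 d².

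The time test has 3 and (82 − 2) × 3 = 240 degrees of freedom and noncentrality

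λ = f² × 82 × 4 / (1 − r) = 61.5 d² / (1 − r).

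| d | r | λ | P(time effect significant) |
|---|---|---|---|
| 0.2 | 0.5 | 4.92 | 43% |
| 0.2 | 0.7 | 8.20 | 66% |
| 0.3 | 0.5 | 11.07 | 80% |
| 0.3 | 0.7 | 18.45 | 96% |

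Simulation with 4,000 trials per row gave 43%, 66%, 81% and 96%. With d = 0 it gave 5.4% (r = 0.5) and 4.7% (r = 0.7), so the test itself behaves correctly. Because λ depends on d², a common decline of the same size gives the same rates.

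**Step 2, the other two terms in the same simulated trials.** Across the four rows the interaction was significant in 4.7% to 5.4% of trials and the group effect in 4.3% to 5.6%. Both stay near 5% because the shift is common to the two arms and cancels in any between-arm contrast.

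**Step 3, dilution of the main group effect.** Suppose the true between-arm difference is 0 at baseline and a constant Δ at the three later visits. The four-visit group effect estimates

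(0 + Δ + Δ + Δ) / 4 = 0.75 Δ.

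It understates the difference by a quarter and cannot create one.

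**Step 4, the second aim against the design.** Whether scores at 12 and 24 weeks after the programme hold up relative to its end can be described from the four visits, in each arm and between arms. Calling those scores gains from the two programmes is a causal statement about each arm alone, and the design has no comparator for it.

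**The case against.** The strongest reply is that section 2.8 merely lists what a mixed ANOVA produces. The main aim is comparative, the Discussion asks whether the game-based form is the better approach, and the sample size rests on the interaction. Nowhere does the article say that a time effect without an interaction will be taken as effectiveness. Much of this stands. Reporting a time effect is ordinary, and the harm lies in a reading that the text permits rather than one it announces. But sections 2.7 and 2.8 both attach the words about the interventions to the time effect, and the second aim attributes gains to both programmes. That is stated wording, not detail left to a document not shown.

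Several stronger readings are tempting and are not supported:

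- **That the randomised comparison is invalid.** It is not. The interaction is reported and kept its nominal error rate in the check.
- **That the percentages are the trial's false-positive rate.** They are the power of the time test against a shift that was put in by assumption. They show that the time test cannot tell treatment from a common shift, not how large that shift will be.
- **That the article declares stroke at any time eligible.** It lists no time limit, which is not the same. The Abstract mentions chronic survivors and functional decline, and participants must be able to walk and manage steps. Early stroke is not excluded, but how much recovery to expect is unknown.
- **That the group effect overstates benefit.** The dilution is conservative.
- **That the second aim cannot be addressed at all.** Maintenance of scores can be described; only its attribution to the programmes lacks support.

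**Conclusion.** The point holds as a fault in stated inference, not in the trial's validity. The plan labels the main time effect, and a group effect averaged over baseline, as effects of the interventions, and the second aim credits sustained gains to each programme. With two active arms, only between-arm differences in change support such claims.

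That conclusion follows from the design and needs no assumed figures. The illustrative range of about 43% to 96% for the time test, against about 5% for the interaction, rests on a common shift of 0.2 to 0.3 SD after baseline, visit correlation 0.5 to 0.7, equal correlations and 82 complete participants. The 75% figure rests on a between-arm difference that is constant after baseline. The wording should be corrected before results are reported.

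**What to change.** - **Section 2.8:** state that conclusions on effectiveness and durability rest on between-arm differences in change from baseline, through the time-group interaction or baseline-adjusted contrasts at the post-baseline visits.
- **Time effects:** report them, and within-arm change, descriptively and without a claim of intervention effect.
- **Main group effect:** do not use the version that includes baseline as evidence of effect.
- **Section 2.7:** align the sentence that describes all three terms as effects of the interventions.
- **Second aim (Abstract and Introduction):** reword it as whether the between-group difference is sustained at 12 and 24 weeks after the trial, with maintenance within each arm as a descriptive addition.

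This needs no extra arm, participants, visits or data. The cost is that fewer favourable statements can be made about each arm alone: if the arms improve equally, the report can say that scores rose in both, but not that either programme caused the rise.

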### Ethics and dissemination

2.9

This study received ethical approval from the National Medical Ethics and Research Committee (NMERC) (study ID: NMRR–20–2715–57464). NMERC, being an independent research committee under the Malaysia Ministry of Health is also responsible in monitoring the study progress. All participants will be asked to provide an informed consent prior to participating in the study by the main researcher. Participants are allowed to withdraw anytime during the study without providing an explanation. Participants’ personal data will be kept confidential. Investigators in this study will have access to the final trial dataset. The findings of this study will only be published in a peer-reviewed journal.

## Discussions

3

Circuit exercise training has been shown to benefit stroke survivors in improving their functional performance through exercising in group under therapists’ supervision. However, evidence on including enriched and fun environment into the existing format of circuit exercise to make it more challenging and interesting particularly for stroke survivors is still limited, which warrants more studies on this topic area. The nature of each exercise task in the designed Checkercise board will offer such targeted environment by adding multisensory stimulation and cueing, cognitive stimulation and limb integration training to further increase neuroplasticity potentials.

Further, the presence of fun and enjoyment through competition could be a factor affecting stroke survivors’ motivation and adherence level during exercise training. We believe that the game-based component of our circuit exercise training will induce these positive influences. Within the fun environment, participants will compete and work hard to achieve their best level exercise performance, hence would induce better functional recovery through enhanced neuroplasticity.

This proposed study is expected to fill the gaps in knowledge and strengthen evidence on the benefit of game-based circuit exercise for stroke survivors. This study will also compare game-based circuit exercise with the existing circuit exercise for stroke survivors and provide information whether game-based circuit exercise is a better approach for this group of population in preventing long-term functional problems. It is our hope that findings from this study can be used to enable rehabilitation professionals to design more interesting, creative and effective exercise training in stroke rehabilitation and serve as a reference for future studies regarding game-based circuit exercise.
